### Assessment of emotions

The Profile of Mood States (POMS) questionnaire is a standard validated psychological rating scale used to determine mood states. Altogether, 35 items of emotions and feelings are recorded at baseline and after each section of a seminar using the POMS as previously described [15]. Briefly, the subject will grade their specific emotions and feelings from “0 as not at all”, “1 as a little bit”, “2 as moderate”, “3 as quite a lot”, and “4 as extremely”. All emotions scores will be calculated to indicate Total Mood Disturbance (TMD). Absolute values and percent change in TMD from baseline will be calculated at each time point of measurement.

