## Subjects and methods

### Study subjects

We will include physically and mentally healthy medical students in the first three years of their six-year medical degree programme. Study subjects with a history of cardiovascular or neurological diseases as well as those that are currently under any medical treatment will be excluded from the study. Furthermore, subjects with addiction to drugs or alcohol, smokers and pregnant subjects will be excluded.

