### Statistical analysis plan

The primary endpoint constitutes a group difference in Standard Deviation of all NN intervals (SDNN). Further endpoints encompass a change of remainder functional parameters of the ANS. The study is conceptualized as a pilot study due to lack of preliminary work. Because of the exploratory nature of this study and absent preliminary research using the same assessment techniques we did not undertake a formal sample size calculation. We intend to allocate 48 subjects (*n* = 48) as targeted sample size.

All statistical calculations will be performed using GraphPad Inplot, ISI software and PRISM Version 5.01 (Graphpad Holdings, LLC, CA, USA). Normality will be assessed by descriptive and analytic methods (Shapiro–Wilk test). Under crossover conditions randomization with a two-period, two-treatment design (2 × 2 design) will be performed. In addition, carryover effects between treatments and periods will be tested using two-way repeated measures ANOVA (mixed model). A two-sided *p* > .05 indicates no carryover effects due to sequencing order. Measured values at each treatment period will then be normalized by mean measured values at baseline. Data include HRV parameters (RMSSD, SDNN, VLF, HF, LF, LF/HF, total power), sudomotor parameters (SCL, SSR), neurovascular function parameters (Δt50%down, Δt50%up, VCR), and pupil dynamics (resting pupil diameter, pupil light reflex amplitude and latency, recovery time, NPi). Between-group differences (baseline vs face-to-face vs videoconference) will be determined using one-way analysis of variance ANOVA followed by Student–Newman–Keul test. Not normally distributed data will be analysed either after log-transformation or *via* non-parametric Friedman two-way ANOVA approach. The significance level is set to alpha = 0.05 and two-sided *p* < .05 is considered significant.

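### Percent change in Total Mood Disturbance is undefined at a zero baseline and unstable near it; the mood comparison should be made in points.

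*Protocol article*

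**What the plan says.** The section Assessment of emotions of the Protocol article describes the Profile of Mood States (POMS): "Altogether, 35 items of emotions and feelings are recorded at baseline and after each section of a seminar". Each item runs from 0 to 4; the wording at the top of the scale is "4 as extremely". The items are then combined into one score, TMD, with no statement of which items are added and which, if any, are subtracted. The summary measures are fixed in one sentence: "Absolute values and percent change in TMD from baseline will be calculated at each time point of measurement". No rule is given for a baseline that is zero, close to zero or negative.

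The section Study protocol places one POMS before the seminar and another after each session, so each student has a single baseline. On who is enrolled, Study subjects says: "We will include physically and mentally healthy medical students".

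The Statistical analysis plan section makes SDNN primary and the other autonomic parameters further endpoints. Its list of data to be analysed does not include TMD. For non-normal data it offers log-transformation or a Friedman analysis. On numbers it says: "We intend to allocate 48 subjects".

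**The concern.** A percentage of baseline is meaningful when zero is a true origin and baselines lie well away from it. A mood score summed from ratings lacks the first property. In a healthy sample it may lack the second.

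Three things can go wrong. A student with baseline 0 has no value and drops out of the summary. A student with a small baseline produces a very large percentage from an ordinary change in points. If the score can be negative, worsening appears as a decrease.

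Mood matters here because the Introduction aims to learn whether autonomic changes translate into differences in learning success and stress levels, and TMD is the only stated summary of the POMS. With points and percentages both planned and neither named as the mood measure, the two could disagree and either could be reported.

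**Working it through.** The article gives no TMD mean, standard deviation or expected difference, so there is no figure of its own to reproduce. The check has four steps.

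**1. Range of the score.** Inputs: 35 items scored 0 to 4 (Assessment of emotions). If all are summed, TMD runs from 0 to 35 × 4 = 140. If k items are subtracted, it runs from −4k to 4 × (35 − k). The value of k is an assumption: k = 5 gives −20 to 120, k = 7 gives −28 to 112, and k = 10 gives −40 to 100. Zero is possible under every rule; negative values are possible only with subtraction. On a plain sum, zero requires the lowest rating on all 35 items, which would be rare.

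**2. The percentage itself.** Percent change = 100 × (follow-up − baseline) / baseline. For the same 4-point worsening:

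- baseline 40: 4/40 = +10%
- baseline 2: 4/2 = +200%
- baseline 0: undefined
- baseline −4 (subtractive scoring only): 4/(−4) = −100%

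**3. The contrast between settings.** Let b be a student's baseline, and F and V the TMD after the face-to-face and videoconference sessions.

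- In points: (F − b) − (V − b) = F − V. The baseline cancels.
- In percent: 100(F − b)/b − 100(V − b)/b = 100(F − V)/b.

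The percentage adds nothing to F − V except a weight of 1/b. A student at baseline 2 gets 40/2 = 20 times the weight of one at baseline 40, and 20² = 400 times in squared terms. This holds even if TMD cannot be negative.

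**4. How much it could matter.** A simulation of 48 students, repeated 4,000 times, looked at change from baseline to one follow-up. All distributional inputs are assumptions: baseline SD 12, true worsening 3 points, SD of change 6. In the signed version baselines may be negative. In the floored version values below 0 are set to 0, which makes zeros commoner than a plain 35-item sum would.

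| Score | Baseline mean | At least one baseline of 0 | Variance carried by the 5 most extreme students, percent scale | Mean percent change has wrong sign |
|---|---|---|---|---|
| signed | 0 | 80% | 79% | 51% |
| signed | 10 | 66% | 82% | 25% |
| signed | 20 | 33% | 82% | 11% |
| signed | 40 | 1% | 56% | 1% |
| floored | 10 | 100% | 78% | 0% |
| floored | 20 | 92% | 74% | 0% |
| floored | 40 | 2% | 56% | 0% |
| floored | 60 | 0% | 48% | 0% |

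On the points scale the five most extreme students carry about 44% to 45% throughout. The distortion is therefore large at assumed baseline means up to about 20 and mostly gone by 40.

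The share of students at or below 0 cannot be pinned down either. For a rounded normal baseline it is Φ((0.5 − mean)/SD). With mean 20 and SD 6 this is Φ(−3.25), about 0.06%; with mean 5 and SD 15 it is Φ(−0.30), about 38%. In 48 students that is anything from none to about 18.

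**The case against.** The strongest reply is that the quoted sentence already plans absolute TMD, which has no denominator, and that no test is tied to percent change in TMD. A reader might infer that the whole mood comparison is uninterpretable, or that it will be driven by the calmest students. The article does not support that: the weakness lies in one of two planned summaries, and dominance by low-baseline students depends on a baseline distribution nobody has stated.

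A reader might also take sign reversal as established. It is not. It needs a subtractive scoring rule, and the article says only "All emotions scores will be calculated to indicate Total Mood Disturbance (TMD"). A condensed article may leave that rule to the full protocol or the cited source.

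Third, if the general analysis rules were applied to TMD, exploding ratios would tend to fail the normality check and could lead to the Friedman analysis. That ranks within student, and dividing by a student's own positive baseline leaves those ranks unchanged. This stands for positive baselines. It does not help at baseline 0, where there is nothing to rank, or below 0, where the order is reversed. The other fallback, log-transformation, fails for zero or negative values; percent change itself is zero or negative for any student whose TMD does not rise.

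Last, this is a non-primary measure in a self-described exploratory pilot. That limits the importance of the point but gives no reason to keep a poor summary when a sound one is already collected.

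**Conclusion.** The point holds in a limited form. Percent change in TMD is a poorly chosen, prespecified summary: undefined at a zero baseline, inflated at low ones (+200% against +10% for the same 4 points at baselines 2 and 40), and adding only a 1/baseline weight to the contrast between settings. These statements follow from the item scale and the single baseline alone.

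Sign reversal is conditional on positive items being subtracted and a baseline below zero. The practical size is unknown: under the assumptions shown, it runs from severe at baseline means of 0 to 20 to slight at 40 and above. Absolute TMD and the SDNN conclusion are unaffected. It is worth changing because the sentence is already fixed and the correction costs almost nothing.

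**What to change.** In Assessment of emotions, delete percent change in TMD and name TMD in points as the mood measure. Report the within-student difference F − V in points with its 95% CI, allowing for period. One simple way is to take the mean of F − V within each sequence group and average the two means, with the interval from the corresponding two-sample calculation. Describe change from baseline in points. Add a clause stating how the 35 items are combined, so that the direction and range of the score are clear.

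The cost is a sentence or two in the protocol, with no extra data or visits. The small loss is a unit-free percentage for readers who do not know the scale; stating the possible range of TMD beside the result largely makes up for it.

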### Statistical analysis plan

The primary endpoint constitutes a group difference in Standard Deviation of all NN intervals (SDNN). Further endpoints encompass a change of remainder functional parameters of the ANS. The study is conceptualized as a pilot study due to lack of preliminary work. Because of the exploratory nature of this study and absent preliminary research using the same assessment techniques we did not undertake a formal sample size calculation. We intend to allocate 48 subjects (*n* = 48) as targeted sample size.

All statistical calculations will be performed using GraphPad Inplot, ISI software and PRISM Version 5.01 (Graphpad Holdings, LLC, CA, USA). Normality will be assessed by descriptive and analytic methods (Shapiro–Wilk test). Under crossover conditions randomization with a two-period, two-treatment design (2 × 2 design) will be performed. In addition, carryover effects between treatments and periods will be tested using two-way repeated measures ANOVA (mixed model). A two-sided *p* > .05 indicates no carryover effects due to sequencing order. Measured values at each treatment period will then be normalized by mean measured values at baseline. Data include HRV parameters (RMSSD, SDNN, VLF, HF, LF, LF/HF, total power), sudomotor parameters (SCL, SSR), neurovascular function parameters (Δt50%down, Δt50%up, VCR), and pupil dynamics (resting pupil diameter, pupil light reflex amplitude and latency, recovery time, NPi). Between-group differences (baseline vs face-to-face vs videoconference) will be determined using one-way analysis of variance ANOVA followed by Student–Newman–Keul test. Not normally distributed data will be analysed either after log-transformation or *via* non-parametric Friedman two-way ANOVA approach. The significance level is set to alpha = 0.05 and two-sided *p* < .05 is considered significant.

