**Statistical Analysis:**

Carryover effects will be handled using a two-way repeated measures (mixed model). Between-group differences (baseline vs face-to-face vs videoconference) will be determined using one-way analysis of variance ANOVA followed by Student–Newman–Keul test.

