### Study protocol

Subjects will complete a questionnaire that contains six standard demographic questions and ten questions regarding their medical history. Each subject will be randomized to participate in two learning methods of a preclinical seminar within the same topic, in the order of face-to-face and then videoconference or vice versa under open-label conditions. For the study measurements, there will be two subjects and two investigators in every seminar. One investigator will monitor one study participant for the whole period of the measurement. One participant will start with the traditional face-to-face learning, while the other participant will start with video conference method. Regarding the randomization, we will be using tossing a coin method as a simple randomization. The coin will be tossed by the researcher and the participant will guess the result as “head” or “tail”. Heterogeneity of population will be subsided since we use each participant as its own control by applying a randomized crossover sequence of experimental seminar phases. During the learning session, the subjects will interact only with the instructor. The investigators will interact with the subjects only to attach the electrodes and transducer and give signal when to change learning settings. Throughout the learning sessions, the participant will interact with the same instructor within the same learning topic. Repeating students will not be enrolled in this study. The student who already joined the study measurement will not be included for another measurement.

All measurements will be performed in a temperature and humidity-controlled environment. Measurement time per subject will last around 100 min. This includes measurement at baseline, during seminar settings, and a 10-minute break between settings. The measurements will take place at the same time of day. The study flow is depicted in Figure 1.

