### Limitations and strengths

This study is limited by its pilot nature. However, the detailed autonomic nervous system phenotyping as well as the randomised crossover design ensure high internal validity. Moreover, the results of this study may help to elucidate how the digital transformation of learning in medicine affects psychophysiological health and form a basis for research in large populations of medical learners to identify most effective learning strategies that utilize digital communication and learning tools. Since this is an exploratory pilot study, we will not undertake any validation study prior to the use of the learning progress test. The test will be designed by the lecturers participating in our study based on their expertise in the field. However, the crossover design of our study will ensure comparability of cohorts as each subject will be their own control. This will also minimize inter-individual variability as well as confounding by factors that affect the physiologic and learning responses of the learners to achieve high internal validity.

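### As written, the primary SDNN comparison is a one-way ANOVA with no student or period term, so its standard error and p-value do not fit the 2 × 2 crossover

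*Protocol article*

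**What the plan says.** All references are to the protocol article.

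- **Design** (Statistical analysis plan): "Under crossover conditions randomization with a two-period, two-treatment design (2 × 2 design) will be performed". Under Study protocol the reason given is that "we use each participant as its own control by applying a randomized crossover sequence of experimental seminar phases", and Limitations and strengths repeats that "the crossover design of our study will ensure comparability of cohorts as each subject will be their own control".
- **Primary endpoint** (Statistical analysis plan): "The primary endpoint constitutes a group difference in Standard Deviation of all NN intervals (SDNN").
- **Test of the setting comparison** (Statistical analysis plan): "Between-group differences (baseline vs face-to-face vs videoconference) will be determined using one-way analysis of variance ANOVA followed by" a Student–Newman–Keuls test. The abstract names the same method: the differences "will be determined using one-way analysis of variance ANOVA".
- **Where a repeated-measures model is named**: only for carryover, where "carryover effects between treatments and periods will be tested using two-way repeated measures ANOVA (mixed model").
- **Non-normal data**: "Not normally distributed data will be analysed either after log-transformation or" by a Friedman test.
- **Normalisation**: session values are divided by mean baseline values before the ANOVA. Whether this is the student's own mean or the group mean is not said.

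**The concern.** Baseline, face-to-face and videoconference are three measurements on the same student. A one-way ANOVA has a single factor and treats them as three independent groups. Between-student variation then stays in the error term, and the own-control advantage for which the crossover was chosen is not used by the stated test. Nor is there a term for first versus second session, although two 40-minute sessions follow each other with a 10-minute break and fatigue or habituation is plausible.

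Because Friedman is a within-student test, whether the pairing is respected would depend on a normality result and on an open choice between two routes. The comparison affected is the primary one. The likely consequence is that a real difference between settings goes undetected, reported with an error estimate that does not describe the design.

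**Working it through.** The article gives no power or sample-size calculation, so there is no figure to reproduce.

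**Inputs from the article.** n = 48 (Statistical analysis plan; the abstract says fifty), two-sided alpha 0.05, 2 × 2 crossover. **Assumed, because not given:** within-student correlation ρ from 0 to 0.8; effects of 0.3 SD, or of 10% with a log-scale SD of 0.4.

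**1. Raw values (or values divided by a group mean, which only rescales them).**

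SE used by the ANOVA = SD·√(2/n) = 0.204 SD. True SE of the contrast = SD·√(2(1−ρ)/n). Their ratio is 1/√(1−ρ). Simulation used 8,000 runs per row and the two-mean comparison on the pooled error. Figures in brackets also require a significant overall F.

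| ρ | SE ratio | Type I error | Power at 0.3 SD, ANOVA | Power at 0.3 SD, student + period model |
|---|---|---|---|---|
| 0 | 1.00 | 5.2% | 31% (22%) | 30% |
| 0.2 | 1.12 | 3.1% | 29% (20%) | 36% |
| 0.5 | 1.41 | 0.7% | 25% (15%) | 53% |
| 0.7 | 1.83 | 0.1% | 19% (10%) | 75% |
| 0.8 | 2.24 | <0.1% | 15% (6%) | 90% |

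The crossover model kept its type I error at about 5% throughout.

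**2. Values divided by the student's own baseline.** Every baseline value becomes 1, so that group has no variance and the pooled error is (0 + s² + s²)/3 = 2s²/3. With r the correlation between the two *normalised* session values, the SE ratio is √(2/3)/√(1−r): 0.82 at r = 0, 0.91 at 0.2, 1.00 at 1/3, 1.15 at 0.5 and 1.49 at 0.7. Simulated type I error is 11%, 7.9%, 5.6%, 2.7% and 0.4%.

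The shared denominator itself creates correlation. On the log scale r = v₀/(v₀ + vₛ), where v₀ and vₛ are the within-student variances of a baseline and a session value. If these are equal, r = 0.5 whatever ρ is, which gives the figure of about 3%. The anti-conservative range r < 1/3 needs v₀ < vₛ/2.

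**3. A 10% difference, ρ = 0.7.** The effect is ln 1.1 = 0.0953.

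- *Paired:* SE = 0.4·√(2·0.3/48) = 0.0447; 0.0953/0.0447 = 2.13; power ≈ Φ(2.13 − 2.01) ≈ 55%.
- *ANOVA, raw:* SE = 0.4·√(2/48) = 0.0816; the threshold is 1.977·0.0816 = 0.161; power ≈ Φ((0.0953 − 0.161)/0.0447) ≈ 7%. Simulation on the unlogged scale gives about 9%.
- *ANOVA, own baseline:* s² = 2·0.3·0.16 = 0.096; pooled error 0.064; SE = √(2·0.064/48) = 0.0516; the threshold is 0.102; power ≈ Φ((0.0953 − 0.102)/0.0447) ≈ 44%. Simulation gives about 43%.

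The full Student–Newman–Keuls sequence, which first requires the range of all three means to be significant, gives about 3–5% (raw) and about 40% (own baseline).

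**4. If repeated measures were intended but period is omitted.** Assume a period effect of 0.5 SD and ρ = 0.7.

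- *Sequences 24/24:* no bias, but the period effect adds 0.5² = 0.25 to the variance of the differences, 2(1−0.7) = 0.6. The SE is inflated by √(0.85/0.6) = 1.19. Simulated type I error is 2.1%, and power at 0.3 SD is 60% against 74% with period in the model.
- *Sequences 19/29:* the contrast is shifted by 0.5·(19−29)/48 = −0.104 SD, close to its true SE of 0.112 SD. Simulated type I error is 7.8%, against 5.0% with period in the model.

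**The case against.** The strongest reply is that the article never calls the ANOVA ordinary or the groups independent. Friedman is the rank counterpart of a one-way repeated-measures ANOVA, and the own-control statements point the same way. A condensed article may simply have dropped the words. That is a fair possibility. It does not settle the matter: the same paragraph uses the repeated-measures term for carryover and not for the setting comparison, the abstract has the same omission, and the kinder reading still leaves out period.

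It is also fair that own-baseline normalisation would already remove much between-student variance, so the raw figures may overstate the loss. Both are therefore shown.

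On period, Study protocol has one member of each pair starting in each setting, which would keep the sequences balanced and the contrast unbiased. The same section also describes a coin toss per participant as simple randomisation, which does not guarantee balance. Even with balance, the test is distorted if a period effect exists.

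Three stronger readings are tempting and not supported:

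- **The choice between a log-scale test and Friedman inflates false positives.** Taking the better of a log-scale repeated-measures test and Friedman gives about 7.6%, but that presupposes the repeated-measures analysis that the text does not name. With the one-way ANOVA it does name, the rate is about 5–6% for ρ from 0.2 to 0.8. Nor does the article say that the smaller p-value will be taken.
- **The setting estimate is biased.** Ignoring student does not bias it; ignoring period does so only with unequal sequences.
- **The pilot's main product, a variance estimate, is lost.** The article says only that results may form a basis for larger research.

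**Conclusion.** The point stands on the text as written: the named primary test has no student and no period term, and its parametric and non-parametric routes do not match. The error is usually conservative. For assumed ρ of 0.5 to 0.8, true type I error is about 0.7% to below 0.1% on raw values, and about 3% or lower with own-baseline division. Power for a 10% difference at ρ = 0.7 is about 9% or 43%, against about 55% paired. It could be anti-conservative under own-baseline division if the two normalised values are only weakly correlated (below about 1/3).

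The sizes rest on an assumed correlation, an assumed log SD of 0.4 and an unclear normalisation rule. The direction of the repair does not depend on them. If repeated measures were intended, what remains is the omitted period term. This should be corrected before analysis because it concerns the primary endpoint.

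**What to change.** In the abstract and in the Statistical analysis plan section, replace the one-way ANOVA with Student–Newman–Keuls for face-to-face versus videoconference by a within-student crossover analysis. A linear mixed model would serve, with setting and period as fixed effects, sequence optional, and student random. Name the setting contrast with its 95% CI as the primary result. State the analysis scale in advance (log SDNN is one option). Say whether normalisation uses the student's own or the group's baseline. Make comparisons with baseline within-student as well.

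Friedman may stay as a within-student sensitivity check, or be replaced by a rank-sum test of the period differences between the two sequences, which also allows for period.

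The cost is a few sentences and a routine model fit. No extra students, visits or measurements are needed.

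### The named analysis of the setting effect (one-way ANOVA, then Student–Newman–Keuls) gives no confidence interval for face-to-face minus videoconference, in a pilot with no sample size calculation

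*Protocol article*

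**What the plan says.** The section 'Statistical analysis plan' of the protocol article makes a group difference in SDNN the primary endpoint and treats the other autonomic parameters as further endpoints. For all of them, the comparison of the three conditions (baseline, face-to-face, videoconference) "will be determined using one-way analysis of variance ANOVA followed by Student–Newman–Keul test". The 'Statistical Analysis' paragraph of the abstract names the same procedure.

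The rule for reading the result is a p-value: "The significance level is set to alpha = 0.05 and two-sided" p < .05 counts as significant. For skewed data, "Not normally distributed data will be analysed either after log-transformation or" by a Friedman test. A repeated-measures mixed model also appears, but its stated job is to test carryover.

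On size and purpose, the same section describes an exploratory pilot and states that "we did not undertake a formal sample size calculation"; the target is 48 students. 'Limitations and strengths' hopes that the results will "form a basis for research in large populations of medical learners".

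**The concern.** A study justified by the absence of preliminary work is most useful if it reports how large the setting effect appears to be, how uncertain that estimate is, and how variable the within-student difference is. The procedure fixed for the setting comparison answers a narrower question: it sorts three condition means into different and not different at the 5% level.

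With no power basis, a non-significant label is a plausible result even when a real effect exists. The label alone does not show which SDNN differences remain compatible with the data. If the report followed the text and stopped there, readers would have a significance statement but no range for the effect, and anyone sizing a later crossover would lack the variance of the relevant contrast.

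**Working it through.** **Inputs.** From 'Statistical analysis plan': n = 48, three conditions, alpha 0.05 two-sided, 2 × 2 crossover. The article gives no SDNN standard deviation, no relevant difference, no within-student correlation and no power figure, so there is no stated figure to reproduce. Results are therefore in SD units, and effect sizes and correlations below are assumptions.

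**Step 1: can SNK be turned into an interval?** The SNK critical difference between two means is q(0.95; r, df) × s / √n, where r is the number of ordered means the pair spans. With three means, the two settings are adjacent (r = 2) if baseline is the lowest or highest mean, and extremes (r = 3) if baseline lies between them.

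| Reading of the one-way ANOVA | df | r = 2 | r = 3 |
|---|---|---|---|
| Unpaired | 3 × 47 = 141 | 2.796/√48 = 0.404 s | 3.350/√48 = 0.484 s |
| Repeated measures | 2 × 47 = 94 | 2.808/√48 = 0.405 s | 3.368/√48 = 0.486 s |

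The yardstick for the setting pair changes with the observed position of the baseline mean. An adjacent pair inside a range already found non-significant is not tested at all. There is no single critical value to invert into a confidence interval, on either reading of the ANOVA.

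**Step 2: does another named step supply one?** The mixed model is given the carryover test, and the log-transformation/Friedman fallback has no interval attached. So no named step does.

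**Step 3: what the design could give.** Let SDd be the SD of the within-student difference. With equal sequence sizes and a period term, df = 48 − 2 = 46.

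- 95% CI half-width: t(0.975; 46) × SDd/√48 = 2.013/6.928 × SDd = 0.291 SDd.
- 95% limits for SDd, as multiples of the estimate: √(46/χ²) with the 0.975 and 0.025 quantiles of χ² on 46 df gives 0.83 and 1.26.

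**Step 4: could a reader rebuild the interval from means and SDs per setting?** If both settings have SD s and correlation ρ, then SDd = s√(2(1 − ρ)), so the half-width is 0.291 × √(2(1 − ρ)) × s:

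| ρ (assumed) | 0 | 0.3 | 0.5 | 0.7 | 0.9 |
|---|---|---|---|---|---|
| Half-width in s | 0.41 | 0.34 | 0.29 | 0.23 | 0.13 |

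Without ρ, the answer varies about threefold (0.41/0.13), so these summaries would not be enough.

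**Step 5: how often would a paired test miss an effect?** Noncentral t, df = 46, noncentrality d√48, with d the true difference in SDd:

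| d (assumed) | 0.2 | 0.3 | 0.4 | 0.5 |
|---|---|---|---|---|
| Power | 27% | 53% | 77% | 92% |

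Power of 80% needs d = 0.413. These figures describe a paired analysis of 48 students, not the planned SNK procedure.

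**The case against.** The strongest reply is that this is an omission. A condensed article need not list every estimate that accompanies a test, naming a post-hoc test does not forbid an interval, and a fuller plan may add one. That is right about the trial as a whole, so the point is limited to the analysis as written. It does not dispose of the point: the text fixes a specific procedure, and no elaboration of SNK produces a matching interval. A fuller plan would have to add or substitute another analysis.

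Several stronger inferences are tempting and are not supported.

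- **A null result could not be interpreted.** This is true only of the SNK label taken alone. The article nowhere says that p ≥ .05 on the setting comparison means no difference. It uses that reading for carryover, which is a separate matter.
- **The within-student SD would be lost.** The mixed model's residual is a within-student variance, and the team will hold the paired data. The article simply does not plan to report it for the setting contrast.
- **The ANOVA ignores the pairing.** The wording leaves this open. The Friedman fallback is a matched-data test, so a repeated-measures one-way ANOVA is a plausible reading. The point here does not depend on which is meant.
- **73%, 47% or 23% of such trials would end as not significant under this plan.** Those are the complements of the paired-test power at chosen effect sizes. The plan's own rate depends on the reading of the ANOVA, ρ and the baseline mean. For example, take the unpaired reading with ρ = 0.5 (so SDd = s), adjacent settings and a true difference of 0.3 s. The chance that the pair exceeds 0.404 s is about P(Z > (0.404 − 0.300)/0.144) = P(Z > 0.72) = 24%, not 53%.
- **The next trial could not be planned.** The article promises a basis for larger research, not variance inputs for a sample size calculation, and the SD can be computed later from the data.

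**Conclusion.** The point holds in limited form. For SDNN and the further autonomic parameters, the only analysis named for the setting effect is a three-condition test ending in SNK at p < .05. It provides no confidence interval for face-to-face minus videoconference, and the model that could provide one is reserved for carryover. For an exploratory pilot without a sample size calculation, intended to inform larger work, an estimate with its interval is the more useful output.

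The gain from changing is an interval of about ±0.29 SDd from the same 48 students, assuming complete pairs, roughly normal differences and equal sequence sizes. The abstract's enrolment of fifty would make it ±0.284, so that discrepancy does not matter here. The power figures in Step 5 rest on assumed effect sizes and only illustrate why a bare non-significant label would say little. This is a weakness in how the effect will be expressed. It does not show that the data will be uninformative or that a null will be misread.

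**What to change.** In 'Statistical analysis plan' and the matching abstract paragraph, replace the one-way ANOVA/SNK step for the setting comparison. Estimate the within-student face-to-face minus videoconference difference from the crossover mixed model with a period term. Report it for SDNN and each further parameter with a 95% CI and the within-student SD. Add a sentence that a p-value of .05 or more will be reported through the CI and not read as absence of a difference. Where log-transformation is used, give the back-transformed ratio with its CI; where a rank method is used, name an interval that goes with it. Comparisons with baseline can be kept as a separate description.

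The cost is small: a change of wording and some added model output, with no new students, measurements or data. The change does not increase the paired power shown above. It makes the uncertainty visible.
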